### Study Procedure

Patients who fulfill all the inclusion criteria and none of the exclusion criteria will be approached for participation. Due to differences in health care implementation across the three participating countries, the logistics of patient recruitment per site might slightly differ.

### Overall Procedure

The health care professional (cardiologist or cardiac nurse) will inform the patient about the study (orally and in writing). Patients who are willing to participate will be provided with an informed consent and will be given ten days to consider their participation. The research assistant will contact the patients by telephone and schedule a face-to-face appointment if they are willing to participate. During the face-to-face meeting, patients will sign the informed consent (together with the researcher) and will fill in the first set of questionnaires (shown in Table 1).

After completing the questionnaires, they will be randomized to either the intervention or “care as usual” group. Patients randomized to the intervention group will be provided with tools (as described in the “Intervention” section) and instructions on how to use them. Relevant tools and/or applications will be installed on patients’ mobile phone by the research assistant such that the patients will only have to charge the devices. One day after the face-to-face meeting, patients will be contacted by the research assistant by telephone to ensure that all devices are properly charged and that the system is functional. The full intervention (as described below) will be provided for three months. During this period patients will be contacted weekly by the research assistant to evaluate their progress (whether they are compliant or not with the treatment, they will receive feedback about progress).

**Table 1 table1:** Questionnaires.

Questionnaire	No. of items N=177	Construct	Assessment (month)		
			0	3	6
Health Promoting Lifestyle Profile [16]	52	Lifestyle	x	x	x
Do Something Different	45	Behavioral flexibility	x	x	x
World Health Organization quality of life questionnaire [17]	26	Quality of life	x	x	x
Unified Theory of Acceptance and Use of Technology [18]	28	Usability of tools; acceptance of tools; willingness to pay^a^			x
EuroQOL questionnaire [19]	5	Cost-effectiveness	x	x	x
Purpose designed^b^	4	Health care consumption	x	x	x
Patient Health Questionnaire [20]	9	Depression	x	x	x
Generalized Anxiety Disorder scale [21]	7	Anxiety	x	x	x
Distressed Personality scale [22]	14	Type D personality	x	x	x
Client Satisfaction Questionnaire [23]	8	Patient perceived satisfaction^a^			x

^a^These 3 constructs will only be assessed in the intervention group.

^b^Designed by the authors.

**Figure 1 figure1:**
[figure not shown]
Study procedure.

After the three months period, the behavior change component (the DSD program) will be terminated. Hence, between months 3 and 6, patients in the intervention group will only be using the devices that were provided to them at baseline. In addition, to decrease patient burden, some of the tools and/or components will be introduced two months after baseline measurement (see Figure 1 for a schematic overview of the study procedure).

Patients will be instructed to fill in the first set of questionnaires during their face-to-face visit at the hospital. At 3 and 6 months, the patients will receive a link (by email) to access the follow-up questionnaires online with the instruction to complete them within ten working days. If they do not complete the questionnaires within the given time, patients will receive up to three reminder phone calls.

Patients who have been randomized to the intervention group will also be contacted between months 3 and 6 to participate in a qualitative survey (if possible with their partner), which will assess additional properties of the usability and acceptability of the tools.

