### Intervention Versus Care as Usual

#### Intervention

The Do CHANGE intervention consists of different components, which can be used to provide care that meets patients’ needs. All patients included in the intervention group will be provided with the following technology: CarePortal, Moves app, Do Something Different (behavioral program), Beddit, Fitbit, blood pressure monitor, COOKiT, and Vire (the Do CHANGE app). In addition, disease-specific tools will only be provided to those who need them (ie, weight scale and/or FLUiT). Based on patients’ primary diagnosis (HF, CAD, or HT) the tools that might be useful will be recommended by the cardiologist. For example, patients with HF will receive a weight scale, since this can assist with monitoring sudden weigh gain, which might be an indication of deteriorating cardiac function. Figure 2 provides a schematic overview of the intervention components. To decrease patient burden, the COOKiT and FLUiT will be introduced to patients two months postbaseline measurement.

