##### COOKiT

COOKiT is a smart spatula that can monitor patients’ cooking behavior (through a motion sensor which indicates whether the spatula is used) and measure the salinity—for both sodium and potassium—of the food that is prepared. The COOKiT has been developed within Do CHANGE and will be provided to patients two months postbaseline measurement.

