##### FLUiT

Particularly for patients with HF the FLUiT will be recommended. FLUiT is a newly developed device in Do CHANGE which can measure fluid intake. FLUiT is a “smart sleeve” which can be wrapped around a cup, bottle or glass, and will gauge the amount of fluid that it contains. It comprises of an accelerometer and a touch sensor to detect when actual drinking occurs and will log the quantity drank. FLUiT will be provided to patients two months postbaseline measures.

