### Statistical Analyses

Data will be analyzed using SPSS (IBM statistics 22) and LatentGold (Version 5.0) [24,25] statistical package. Continuous and discrete variables will be compared using respectively Students’ t-test and Chi-square test. The Linear Mixed Models (LMM) procedure will be performed to evaluate the treatment effectiveness over time. The LMM procedure is similar to linear regression analyses except that in LMM the dependent variable is measured at multiple time points. These analyses will be adjusted for baseline distress levels. If the interaction effects are not significant, only the main effects will be entered in the final model. To examine which patients might benefit from the intervention based on their profiles, Latent Class Analyses will be performed [26,27]. An alpha of .05 will be used to indicate level of significance.

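### Dropping a nonsignificant arm-by-time interaction would merge the month-3 and month-6 effects into one, although DSD stops at month 3

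*Protocol article*

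**What the plan says.** **Timetable.** Overall Procedure says: "The full intervention (as described below) will be provided for three months". The text after Figure 1 adds that after this period "the behavior change component (the DSD program) will be terminated", and that "between months 3 and 6, patients in the intervention group will only be using the devices that were provided to them at baseline". The Do Something Different section gives DSD a length of 11 weeks. The Intervention section states that, to limit burden, "the COOKiT and FLUiT will be introduced to patients two months postbaseline measurement". COOKiT goes to every intervention patient and FLUiT only to those who need it. The Discussion gives the device period as six months.

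**Assessments.** Table 1 places the lifestyle, behavioral flexibility and quality-of-life questionnaires at months 0, 3 and 6.

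**Analysis.** The Statistical Analyses section says that a linear mixed model "will be performed to evaluate the treatment effectiveness over time". It then states the reduction rule: "If the interaction effects are not significant, only the main effects will be entered in the final model". Alpha is .05. The section does not name the interaction. Since the model is there to assess effectiveness over time, arm by time is the natural reading and is assumed here.

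**The concern.** The two follow-up visits answer different questions about one randomized strategy. At month 3, DSD has just ended. At month 6, patients have had about three months without it while devices continue. The Introduction presents the three-month program as a route to lasting change in health behavior, and the randomized evidence on that is the arm difference at month 6, read beside the one at month 3.

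Under the stated rule, the final model keeps those two differences apart only if the interaction test is significant. Otherwise it contains one treatment effect averaged over visits. A nonsignificant test with 125 per arm is weak evidence that an effect has not faded, and the rule acts most often when effects are small. The Introduction itself says that reported effects of remote interventions have been small. The risk is that the final model overstates the month-6 effect, understates the month-3 effect, and gives no direct estimate of persistence.

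**Working it through.** There is no stated power or effect figure to reproduce: the Sample Size section says that no calculation was done.

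**Inputs from the article.** 125 patients per arm; alpha .05 (taken as two-sided); visits at months 0, 3 and 6.

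**Assumptions.** Outcome SD 1, compound symmetry with correlation ρ = 0.6 (range 0.5 to 0.7), no dropout, and an effect that halves between month 3 and month 6.

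**Interaction test.** Let d be the arm differences at the modelled visits. With v = (2/125)(1 − ρ), the noncentrality is Σ(d − mean d)²/v, with degrees of freedom equal to the number of visits minus 1. At ρ = 0.6, v = 0.016 × 0.4 = 0.0064.

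| Model | d | Σ(d − mean d)² | Noncentrality | Dropped, ρ = 0.6 | Dropped, ρ = 0.5 to 0.7 | Merged effect |
|---|---|---|---|---|---|---|
| Follow-up only, 1 df | 0.2, 0.1 | 0.005 | 0.78 | 86% | 82-88% | 0.15 SD |
| Follow-up only, 1 df | 0.4, 0.2 | 0.020 | 3.125 | 58% | 47-65% | 0.30 SD |
| With baseline, 2 df | 0, 0.2, 0.1 | 0.020 | 3.125 | 67% | 57-73% | 0.10 SD |
| With baseline, 2 df | 0, 0.4, 0.2 | 0.080 | 12.5 | 10% | 4-18% | 0.20 SD |

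The merged effect is the mean of d, for example (0.2 + 0.1)/2 = 0.15, or (0 + 0.2 + 0.1)/3 = 0.10.

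**Other fading patterns.** With baseline as an outcome visit and ρ from 0.7 to 0.5, the interaction is dropped in 20-43% of trials for 0.3 falling to 0.1 SD, 10-31% for 0.3 falling to 0, and 3-15% for 0.4 falling to 0.1.

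**Dilution by baseline.** Suppose the effect does not fade: 0.2 SD at both follow-up visits. With baseline as an outcome visit, the main effect is (0 + 0.2 + 0.2)/3 = 0.13 SD. At ρ = 0.6, Σ(d − mean d)² = 0.0267 and the noncentrality is 0.0267/0.0064 = 4.17, so the interaction is dropped in 57% of trials. This dilution is separate from the end of DSD.

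**Accuracy under the rule** (follow-up only, ρ = 0.6, simulated):
- 0.2 falling to 0.1 SD: mean squared error at each visit is 0.0162, against 0.0160 when the visits are always reported separately. If the merged effect is read as a visit's own effect, nominal 95% CIs cover about 92% of the time.
- 0.4 falling to 0.2 SD: 0.0202 against 0.0160, with coverage of about 89%.

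**Precision of separate reporting** (ρ = 0.6). One visit: √(2/125) = 0.126 SD. Mean of two follow-up visits: √((2/125)(1 + 0.6)/2) = 0.113 SD. The ratio is 1.12.

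**The case against.** **The staging is deliberate and disclosed.** This stands. An active phase followed by reduced support is an ordinary design, and the mean over two visits is a legitimate summary of one strategy. A reader might infer that the changing package invalidates the comparison. It does not: the arm difference at each visit is a valid randomized contrast.

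**The rule governs the final model, not what is reported, and a SAP may add contrasts.** This stands in part. The interaction model is fitted first, and visit-specific contrasts could still be reported. But the article does more than leave this open: it fixes which model is final, and a SAP would have to reverse that.

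**The magnitudes are assumed.** This stands. The drop rate runs from 3% to 88% across the scenarios. In the scenario with the highest rate, 0.2 falling to 0.1 SD with follow-up visits only, the accuracy cost is small: about 1% in mean squared error, and a merged effect 0.05 SD away from each visit's true effect.

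**Baseline dilution is a different problem.** This also stands. Much of the fall from 0.2 to 0.10 SD in the three-visit case comes from averaging in baseline, since a constant 0.2 SD already becomes 0.13 SD.

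**The timetable wording.** A reader might infer that the article contradicts itself, because three months of full intervention does not fit with "will be provided to patients two months postbaseline measurement" for COOKiT, and restricting months 3 to 6 to baseline devices would exclude COOKiT and FLUiT. The documents do not support more than loose wording. The Intervention, COOKiT and FLUiT sections give the month-2 start, the sentence after the restriction repeats staged introduction, the Discussion has devices running for six months, and Figure 1 is not shown.

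**Conclusion.** The concern holds for the reduction rule, read as arm by time. The rule lets a test that often has low power decide whether the effect at the end of DSD and the effect three months later are estimated separately, and a nonsignificant result does not show that they are equal. With effects halving from 0.2 SD, the interaction would be dropped in 82-88% of trials (follow-up visits only) or 57-73% (baseline as an outcome visit). Halving from 0.4 SD gives 47-65% or 4-18%. These figures rest on assumed effects, correlations and complete data. The loss is mainly in what the final model describes, since the cost in mean squared error ranges from about 1% to about 26% (0.0202/0.0160) in the two cases simulated.

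A reader might also infer that month 6 isolates the devices. It does not: those patients received DSD first, and carry-over from it is part of what month 6 measures. The staging is sound, and the Overall Procedure wording is an editorial matter only.

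**What to change.** In Statistical Analyses, replace the reduction rule: keep arm by visit in the final model whatever its p-value, and report the arm difference with 95% CI at month 3 (end of DSD) and at month 6 (three months after DSD ended, devices continuing). Describe both as effects of the whole randomized strategy, not of devices alone. Separate estimates also remove the dilution that arises when baseline is an outcome visit.

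The cost is a standard error of 0.126 SD at one visit, against 0.113 SD for the mean of the two follow-up visits at correlation 0.6, about 12% wider. No visits, devices or patients are added, and the month-2 introduction stays as planned. As an optional edit, Overall Procedure could list which components run in months 0-2, 2-3 and 3-6.

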### Study Objectives

Primary, secondary and exploratory objectives will be assessed as described below.

#### Primary Objectives

Primary objectives of the trial include: 1) lifestyle (eg, sleep, physical activity, nutrition) change and disease management; 2) enhancement of quality of life; and 3) change in behavioral habits and personal flexibility. The assessment of these objectives will be performed using standardized and validated questionnaires (Table 1). In addition, purpose designed questionnaires will be administered to evaluate changes in objective #3. Furthermore, objective measures (ie, data from devices used by the intervention group) will be employed to evaluate changes in lifestyle variables. However, this will be done only within the intervention group since the “care as usual” group will not receive any devices.

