## Discussion

Cardiovascular diseases are the leading cause of death globally, and they pose a significant burden on current health care systems [1,28]. Studies have shown that behavioral factors (eg, physical inactivity, unhealthy diet) account for a large proportion of the disease burden and thus should be addressed (potentially) by health care providers [2]. The Do CHANGE trial aims to address lifestyle behaviors and increase the quality of life of patients with CAD, HF, and HT. By increasing patients’ behavioral flexibility and providing them with supportive devices, patients are expected to break with their unhealthy habits and change their unhealthy lifestyle in a sustainable manner.

According to Pine & Fletcher [13] there are multiple reasons why current behavioral programs have not been successful in changing health behaviors. Firstly, our behavior is only partly guided by willpower, hence, most patients fail to use willpower to prevent habitual behaviors (eg, smoking). Secondly, behavior is often guided by everyday environmental cues which trigger certain response (eg, having a beer triggers smoking). Finally, there is a knowledge-doing gap which is demonstrated by the fact that we often know what is good for our health but we fail to do it [12,13]. People tend to live by their habits, which can be stable over time, and seem not to be able to act in accordance with their knowledge. Hence, within Do CHANGE, we aim to increase awareness and knowledge about unhealthy behaviors and at the same time, by using the DSD technique, disrupt habit chains in daily living. This is expected to boost behavioral flexibility and enhance behavior change [15].

A total of 250 patients will be recruited from three pilot sites (Spain, The Netherlands, and Taiwan) and will be randomized to either the intervention group or care as usual. Patients in the intervention group will receive the DSD program (for three months) and will be using devices that will assist them in behavior change (for 6 months). Patients will be assessed at baseline, and at the third and sixth months.

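### Three unranked primary objectives share one alpha of .05 with no stated success rule; if any one result suffices, the chance of a false-positive primary result is up to about 14% instead of 5%

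*Protocol article*

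**What the plan says.** The section Primary Objectives begins: "Primary objectives of the trial include: 1) lifestyle (eg, sleep, physical activity, nutrition) change and disease management; 2) enhancement of quality of life". The list ends with "3) change in behavioral habits and personal flexibility". No order of importance is given and no single primary outcome is picked out. For the third objective there is more than one measure: "In addition, purpose designed questionnaires will be administered to evaluate changes in objective #3".

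Table 1 schedules the lifestyle, flexibility and quality-of-life questionnaires at months 0, 3 and 6, and the Discussion confirms it: "Patients will be assessed at baseline, and at the third and sixth months". Neither follow-up visit is designated as the primary one.

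Statistical Analyses gives the method: "The Linear Mixed Models (LMM) procedure will be performed to evaluate the treatment effectiveness over time". It adds a model-reduction rule: "If the interaction effects are not significant, only the main effects will be entered in the final model". The error rule is one sentence: "An alpha of .05 will be used to indicate level of significance". It does not say whether .05 applies to each test or to the primary objectives as a set, and it states no hierarchy, split or adjustment.

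The Introduction says that the trial is meant to evaluate effectiveness. Sample Size calls it a proof of concept and declines a sample size calculation.

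**The concern.** A reader of the results will want to know whether the service worked. The article offers three primary objectives that could answer, and does not say in advance what pattern of results would count as a yes. A significant result on any of the three could then be reported as meeting a primary objective, at a level that no longer describes the error rate of the overall conclusion.

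The visit matters as well. The behavior change program stops after month 3 and only the devices continue to month 6, so the two visits answer different questions. With outcome, visit and contrast all open, the result that supports the effectiveness claim can be chosen after the data are seen.

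**Working it through.** **The plan's own figures.** The article states no family-wise error rate and no power, so there is no design figure to reproduce other than alpha = .05. Its enrolment arithmetic is consistent: 75 + 100 + 75 = 250; 250/2 = 125 per arm; 250/0.5 = 500 approached.

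**Inputs.**
- From the article: alpha .05 (Statistical Analyses); three primary objectives (Primary Objectives); two follow-up visits (Table 1, Discussion); 125 per arm (Sample Size).
- Assumed, because not given: two-sided tests; one test per objective; no true effect on any outcome; success means at least one significant result. Correlations between test statistics are not given either, so a range is shown.

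**Three tests, one per objective.**
- Either direction, independent: 1 − 0.95³ = 14.3%.
- Benefit only, independent: 1 − 0.975³ = 7.3%.
- With correlation, by multivariate normal simulation with 1,000,000 draws per setting:

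| Correlation between outcomes | Any false positive | False benefit only |
|---|---|---|
| 0 | 14.3% | 7.3% |
| 0.5 | 12.6% | 6.3% |
| 0.7 | 10.9% | 5.5% |
| 0.9 | 8.4% | 4.2% |
| Benchmark: one test | 5% | 2.5% |

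At independence the inflation is 14.3/5 = 2.9-fold, and likewise 7.3/2.5 = 2.9-fold.

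**If months 3 and 6 were tested separately (a reading, not stated).** Six tests:
- Independent: 1 − 0.95⁶ = 26.5% in either direction; 1 − 0.975⁶ = 14.1% for benefit only.
- Correlation 0.5 between outcomes and 0.5 between visits: 22.0% and 11.1%.
- Correlation 0.7 between outcomes and 0.7 between visits: 17.6% and 8.8%.

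**The reduction rule that is stated.** Testing the interaction and, if it is not significant, the main effect gives up to two chances per outcome. If the two steps are taken as independent (as for the difference and the average of two visits with equal variances), the chance of any false positive over three outcomes is about 26.5% with uncorrelated outcomes, 23.5% at correlation 0.5 and 20.7% at 0.7. This rule takes the place of per-visit tests, so these figures are not to be added to the six-test figures.

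**Price of adjustment.** Detectable difference at 80% power, 125 per arm, no dropout: d ≈ (z for alpha + 0.842) × √(2/125), with √(2/125) = 0.1265.
- Alpha .05: (1.960 + 0.842) × 0.1265 = 0.354; 0.356 with the t distribution.
- Alpha .05/3 = .0167: (2.394 + 0.842) × 0.1265 = 0.409; 0.412 with the t distribution.

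**The case against.** **Scope.** This is a condensed article, and an unseen analysis plan may hold the multiplicity procedure. Holm also runs at an overall .05, so the alpha sentence does not rule it out. The proof-of-concept label weakens the case for a strict confirmatory standard. These points stand and lower the severity. They do not remove the issue: the article itself fixes three primary objectives, one alpha and a reduction rule, it states an effectiveness aim, and choosing the primary outcome is a protocol-level decision.

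**No success rule is stated.** This is correct. If all three objectives had to be significant, there would be no inflation. The figures above are conditional on the any-one rule, which the article neither adopts nor excludes.

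**Stronger readings that the article does not support.**
- A reader might infer that a useless intervention has a 14% to 26% chance of a primary success. Those values assume independent tests and count results in the harmful direction. These are questionnaires from the same patients, so positive correlation is likely, and false benefit alone is about half as frequent.
- A reader might count six primary tests. The article plans a mixed model over time, and a group-by-time interaction can be one joint test across both visits. Six is not a firm ceiling either, since objective 1 spans several lifestyle domains and objective 3 has more than one questionnaire.
- A reader might treat "change in behavioral habits and personal flexibility" as the easiest outcome and little more than a check that the program was delivered. The article does present flexibility as the route to behavior change, and the scale carries the program's name. But nothing in it quantifies how easily that scale moves, and flexibility is openly an aim of the trial. Demoting it would be a design preference.

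**Conclusion.** The concern holds in a limited form. The article leaves the primary outcome, the visit and the success rule open while setting one alpha of .05. If any one of three tests suffices, the chance of a false-positive primary result is up to about 14% in either direction (about 11% to 13% at correlations 0.7 to 0.5), against 5%. For false benefit it is up to about 7% (5.5% to 6.3%), against 2.5%. This rests on two-sided tests, one test per objective and an any-one rule. Values near 26% and 14% need further assumptions: separate, independent tests at each visit. The stated interaction-then-main-effects rule is a second way to two chances per outcome. In every setting tried, the error rate stays above that of a single test. The point is a should-fix.

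**What to change.** Before results are seen, do one of the following and state it in the protocol.

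1. **Fixed sequence.** Name one primary outcome, one visit and one contrast, for example the between-group difference in the Health Promoting Lifestyle Profile total at month 6. Test the other two objectives afterwards in a stated order, each at .05, stopping at the first non-significant result. This costs no power on the first outcome.
2. **Keep all three primary.** Name one measure for each objective and one visit or contrast, and apply Holm across the three (.0167, .025, .05). At its first step the detectable effect rises from about 0.36 to 0.41 SD (125 per arm, 80% power, no dropout).

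Under either option, the named contrast should be tested whether or not the interaction is significant, so that the reduction rule does not offer a second chance. If the intention is that all three objectives must succeed, saying so would settle the error-rate question without adjustment. The change is one of wording; data collection is unaffected.

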#### Exploratory Objectives

The current trial will also cover a number of exploratory objectives where the focus will be on 1) identifying subgroups of patients who might benefit the most from this intervention based on their profile (eg, psychological and/or disease profile); 2) evaluating the effects of the intervention on the electrocardiogram (ECG) data; and 3) gaining more insight in patients sleep patterns and physical activity over a prolonged period of time. These objectives will mainly serve the development of our new hypothesis regarding successful lifestyle change and will be tested using latent class analysis (LatentGold 5.0).

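### The planned effect of the intervention on ECG cannot be estimated, because only the intervention arm has an ECG source; other device data likewise show only within-arm course

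*Protocol article*

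**What the plan says.** All places are in the Methods of the protocol article.

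- **Primary Objectives.** The first objective is "1) lifestyle (eg, sleep, physical activity, nutrition) change and disease management". For all three primary objectives, "The assessment of these objectives will be performed using standardized and validated questionnaires (Table 1"). Device data are then added: "objective measures (ie, data from devices used by the intervention group) will be employed to evaluate changes in lifestyle variables". The next sentence restricts this: "this will be done only within the intervention group since the “care as usual” group will not receive any devices".
- **Exploratory Objectives.** The second objective is "evaluating the effects of the intervention on the electrocardiogram (ECG) data". The exploratory objectives are said mainly to serve the forming of hypotheses, and "will be tested using latent class analysis (LatentGold 5.0").
- **Overall Procedure.** Patients complete the baseline questionnaires, are then randomised, and those in the intervention group are then given the tools.
- **Intervention and CarePortal.** The devices are listed as components of the intervention. The CarePortal, installed in the homes of the intervention group, gathers the ECG.
- **Statistical Analyses.** Treatment effectiveness over time is assigned to linear mixed models, with alpha .05. The section does not say which measures count as effectiveness measures.

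**The concern.** An effect of an intervention is a contrast between what happened with it and what would have happened without it. In this trial the randomised usual-care group supplies that second part. For ECG the group supplies nothing, so the objective as worded asks a question that the data cannot answer.

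The lifestyle data from the devices share the gap. Change within one arm mixes any effect of the programme with season, regression to the mean, reaction to being monitored, and selective wearing of the device. The first reading is already taken under the intervention, so there is no clean starting point either. The article states the restriction to one arm but draws no consequence from it: it does not call these data descriptive or keep them apart from the evidence on effectiveness. A favourable trend in activity or sleep could then be reported under a primary objective of a randomised trial, where readers would take it for a randomised result.

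**Working it through.** **Can an effect on ECG be estimated?**

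1. ECG source: the CarePortal section is the only place that describes collection of ECG.
2. Who has it: that section gives the device to the intervention group, and Primary Objectives says that the usual-care group receives no devices.
3. Table 1, the schedule of measures that covers both arms, holds questionnaires only.
4. So ECG data are described for one arm only. Latent class analysis can sort patients within that arm into groups, but it does not supply the missing comparator.

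**Is there a pre-intervention device reading?**

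1. The order in Overall Procedure is questionnaires, randomisation, then tools.
2. The tools are themselves components of the intervention, and Fitbit data trigger some of the behavioural prompts.
3. The behaviour programme lasts 11 weeks within a three-month period of about 3 × 365.25 / 12 / 7 = 13.0 weeks. That could leave about 2 weeks of device use without prompts. Even so, those readings would be made under part of the intervention, and no run-in is described.
4. So no device reading precedes the intervention.

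**How easily could drift be misread?** The plan has no figure of its own to reproduce here: it gives no SD, effect size or power. The following is an illustration.

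- From the article: n = 125 in the intervention arm (Sample Size); alpha = .05 (Statistical Analyses), taken as two-sided.
- Assumed: true intervention effect zero; background drift d, in SD units of the change score, that any patient would show; a simple test of mean change against zero. The article does not specify such a test for device data.
- Formula: probability of significance = Φ(d√n − 1.96) + Φ(−d√n − 1.96), with √125 = 11.18.

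| d | d√n | Probability, n = 125 | Probability, n = 100 |
|---|---|---|---|
| 0 | 0 | 0.05 | 0.05 |
| 0.1 | 1.118 | 0.201 | 0.170 |
| 0.2 | 2.236 | 0.609 | 0.516 |
| 0.3 | 3.354 | 0.918 | 0.851 |

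The n = 100 column shows the result if only 100 patients gave usable data. A simulation of 20,000 trials with t-tests agrees for n = 125: 0.197, 0.604 and 0.916 for d = 0.1, 0.2 and 0.3. When the same drift is put into two arms of 125 and the arms are compared, the simulated rejection rate stays at 0.048 to 0.055, because the drift cancels.

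**The case against.** The strongest reply is that the article is open about the limit. It assigns the primary objectives first to questionnaires, adds the device data as a supplement, speaks of changes and not of effects, and says "However, this will be done only within the intervention group". The lifestyle, quality-of-life and flexibility questionnaires run in both arms at months 0, 3 and 6. The ECG objective is exploratory and meant to generate hypotheses. All of this stands, and it lowers the severity. It does not make an effect on ECG estimable, and it does not say what the device data may be used to conclude.

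The illustration also needs care. If patients truly drift, a significant within-arm change is a correct finding of change; the probabilities above are power to detect that drift. They become rates of error only when the change is credited to the intervention. The drift is assumed, and the width of the range shows how much depends on it.

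Three stronger readings are tempting, and the documents do not support them:

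- A reader might infer that device change will be presented as a treatment effect on a primary outcome. The article does not say so; explicit causal wording appears only for ECG.
- A reader might infer a faulty change-from-baseline analysis for COOKiT, which "will be provided to patients two months postbaseline measurement", and for FLUiT, which starts at the same time. No such analysis is stated for either device.
- A reader might infer that disease management, named in the first primary objective, rests on one-arm device data. The article uses device data for lifestyle variables only. Which Table 1 instrument covers disease management is a separate question of outcome definition.

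**Conclusion.** The point holds in two parts. First, exploratory objective 2 promises an estimate of an intervention effect that the described design cannot give. This follows from the text and needs no assumption beyond the CarePortal being the only ECG source, as described. Second, the device data offered as supplementary evidence on lifestyle change have neither a control group nor a pre-intervention reading, so they can describe the course in the intervention arm but cannot be attributed to the intervention.

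Under the stated assumptions, drift of 0.1 to 0.3 SD alone would be significant within the arm in about 20% to 92% of trials, against about 5% for a randomised comparison of the same data. This shows the scope for misreading; it is not an error rate of the planned analysis. Severity is minor to moderate, since the two-arm questionnaire evidence for the primary objectives is untouched.

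**What to change.** 1. Reword exploratory objective 2 so that it describes the course of the ECG within the intervention group over the period of device use.
2. Add to Primary Objectives that device data are descriptive, covering device use and within-arm course, and that conclusions on effectiveness rest only on the between-arm comparisons of the questionnaires.

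Data collection, sample size and patient procedures stay as they are, so the cost is two changes of wording. The downside is that the sponsor gives up a claim from objective data, but it is one that the design cannot support.
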